### Statistical methods

#### Efficacy evaluation

The efficacy of the Emotion Detectives In–Out in comparison with the Coping Cat will be assessed by analyzing the changes in the primary and secondary outcomes. As an equivalence clinical trial, the aim is to test whether the Emotion Detectives In–Out (experimental condition) is as effective as the Coping Cat (control group). The planned analysis for each outcome is a repeated-measures linear mixed model adjusted for covariates. The primary equivalence testing will be the between-group difference TOST at postintervention and at 3 months using the Welch correction for heterogeneous variance if needed. We will also investigate the linear and nonlinear (quadratic) effects for time and condition and simple effects for parameter estimates within each condition. For categorical variables (e.g., treatment response as assessed by CGI-I), treatment conditions will be compared using Pearson’s chi-square test.

To examine for heterogeneous intervention response, we will calculate Reliable Change Indices (RCI) for all participants at postintervention and at the 3-month follow-up. The RCI will be calculated for all outcomes and correlated with demographics to examine for subgroup efficacy predictors. The cutoff for clinically significant change is generally accepted as ± 1.96 [81]. Likewise, we aim to test the longitudinal trajectory of anxious symptoms over time using Growth Mixture Modeling (GMM). Furthermore, assuming that heterogeneous trajectories of anxious symptoms are observed, we aim to test the suitability of the collected demographic variables as predictors of group membership.

For the primary equivalence, efficacy, RCI, and chi-square analyses, we will use Jamovi software and the GAMLj and TOSTER packages as needed [82]. For GMM analyses, we will use R software with the package *lccm* [83] to perform growth mixture modeling, and evaluate various model specifications of *k* classes two through six, and using both fixed and random effects. We will select the optimal number of clusters was based on four criteria: parsimony, entropy approaching 1, lowest BIC/SABIC, and minimum class size > 10% of the sample [84, 85].

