#### Planned and post hoc examination of potential confounds and moderator effects

##### Covariates

Variables that are expected to correlate with but not predict outcomes differentially will be included in the baseline model to account for their effect. The targeted covariates include sociodemographic and clinical variables, such as the children’s age and sex, number of comorbid disorders, use of psychopharmacological medication, and previous psychological treatment.

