##### Planned moderation analysis

Some variables will be analyzed as moderators of the efficacy of the Emotion Detectives In–Out in the primary and secondary outcomes, including the parents’ and children’s motivation to participate in the intervention, the frequency of homework assignments, both parents’ and children’s involvement in therapy, parents’ perceived barriers to the intervention, and both parents' and children's self-efficacy and enjoyment in using the internet and technology.

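### Correlating the RCI with demographics without an arm term identifies predictors of change under either program, not predictors of subgroup efficacy

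*Protocol article*

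**What the plan says.** In the protocol article, Statistical methods, Efficacy evaluation, the aim of the step is given as follows: "To examine for heterogeneous intervention response, we will calculate Reliable Change Indices (RCI) for all participants". The analysis is then stated: the index is obtained for every outcome and "correlated with demographics to examine for subgroup efficacy predictors". No arm term, arm-by-demographic interaction or between-arm comparison of correlations is mentioned. The growth mixture modelling in the same paragraph also uses demographics without arm: "we aim to test the suitability of the collected demographic variables as predictors of group membership".

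Two later sections bear on the point. Covariates says: "Variables that are expected to correlate with but not predict outcomes differentially will be included in the baseline model". Child age and sex are among its examples. Planned moderation analysis says: "Some variables will be analyzed as moderators of the efficacy of the Emotion Detectives In–Out in the primary and secondary outcomes". The variables it goes on to name are motivation, homework, involvement in therapy, perceived barriers, and self-efficacy and enjoyment with technology. No demographic is named.

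The Objectives section is broader. It speaks of finding factors that may predict adherence and treatment outcomes.

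**The concern.** Efficacy evaluation opens by defining the efficacy of the new program relative to Coping Cat. A predictor of efficacy in that sense is a characteristic that changes the difference between the programs. A child's RCI is not that difference. It combines program effect, natural course and regression to the mean, and there is no untreated arm against which to remove the last two. Only the contrast between arms isolates something due to a program.

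Followed as written, the step would attach an efficacy label to variables that are merely prognostic. Covariates expects such variables to exist and gives age and sex as examples. A reader could then take a finding such as younger children improving more as a reason to prefer one program for younger children, which the analysis cannot support.

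**Working it through.** **Inputs.** From Sample size: 138 children, 69 per arm, 1:1 allocation, margin d = 0.50, alpha 0.05, 80% power. The document gives no slopes of change on demographics, so those below are assumptions.

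**1. The plan's own figure.** For two one-sided tests with a true difference of zero, n per arm = 2 x ((z0.95 + z0.90)/0.50)^2 = 2 x ((1.645 + 1.282)/0.50)^2 = 68.5, so 69 per arm and 138 in total. The stated size reproduces and is not in dispute.

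**2. What the correlation estimates.** If every child's change on a scale is divided by the same constant, the correlation of the RCI with a characteristic equals the correlation of the change score with it. Let the slope of change on the characteristic be b in one arm and b + k in the other, where k is the differential effect. With equal arms, the slope over all children is about (b + b + k)/2 = b + k/2. One number cannot separate b from k.

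**3. Rejection rates.** 20,000 simulated trials per row, 69 per arm, standardized characteristic, residual SD 1, two-sided 0.05:

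| Slopes in the two arms | Mean overall r | Overall correlation flags | Arm interaction flags |
|---|---|---|---|
| 0 and 0 | 0.00 | 5% | 5% |
| 0.3 and 0.3 (prognostic only) | 0.29 | 93% | 5% |
| 0.45 and 0.15 (mixed) | 0.28 | 93% | 41% |
| 0.6 and 0 (one arm only) | 0.28 | 90% | 93% |
| 0.3 and 0 (one arm only) | 0.15 | 41% | 40% |
| 0.3 and -0.3 (opposite) | 0.00 | 6% | 93% |

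Hand check of the second row: r = 0.3/sqrt(1 + 0.09) = 0.287. Fisher z = 0.295, and 0.295 x sqrt(138 - 3) = 3.43. Power is about Phi(3.43 - 1.96) = 93%.

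A second simulation (4,000 trials per scenario) set the within-arm correlation itself to 0.3. Equal correlations gave 95% for the overall correlation and 5% for the interaction. Opposite signs gave 6% and 94%.

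Rows two to four are the telling ones. All three have an average slope of 0.3 and look nearly alike to the overall correlation, yet the differential effect k is 0, 0.3 and 0.6 in size.

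**4. What an interaction test could detect.** For a binary characteristic split 50/50, the standard error of the interaction in SD units is sqrt(16/138) = 0.341. The interaction detectable with 80% power is (1.960 + 0.842) x 0.341 = 0.95.

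**5. Whether another section supplies the test.** Planned moderation analysis names no demographic. Covariates treats age and sex as not differentially predictive. The growth mixture step has no arm. No section states an arm-by-demographic comparison.

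**The case against.** The strongest reply is that the step was never meant to choose between programs. Its stated aim is heterogeneity of response, the Objectives speak of predicting outcomes, and asking which children improve under two active treatments is coherent. That stands: for outcome prediction the correlation is usable. The output label is then wrong, because the same section defines efficacy comparatively.

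A second reply is that the moderator list is introduced as open and that age and sex were deliberately placed among the non-differential covariates. This explains why no interaction is named. It also sharpens the inconsistency, since Efficacy evaluation then searches demographics for efficacy predictors.

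Third, the text does not say that the arms are pooled. It says only "we will calculate Reliable Change Indices (RCI) for all participants at postintervention and at the 3-month follow-up". Pooling is the plain reading, but an inference. Separate within-arm correlations would not rescue the label, because a differential claim still needs a formal comparison of the arms.

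A reader might infer that the correlation always misses differential effects or carries no information on them. The working does not support that. They are missed only when the arm slopes roughly cancel, which is an extreme case for two cognitive-behavioral programs that both include exposure. A one-arm effect is flagged about as often as by the interaction test (41% against 40%; 90% against 93%), but cannot be attributed to a program.

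**Conclusion.** The point holds as a mismatch between a stated method and its stated interpretation, not as missing detail. The RCI correlations identify predictors of change under either program. On assumed slopes of 0.3 with 69 per arm, a variable with no differential effect would be reported as an efficacy predictor in about 93-95% of trials, against about 5% with an arm interaction. An opposite-sign effect would be flagged in about 6%. These rates depend on the assumed slopes; the algebra in step 2 of the working does not.

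The consequence is limited to a secondary, exploratory analysis. A reader might infer that the trial's main conclusion is at risk. It is not: the primary equivalence test and the sample size of 138 do not depend on this step.

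**What to change.** 1. In Efficacy evaluation, describe the RCI correlations as predictors of change irrespective of arm (prognostic), in line with the Objectives. This costs one sentence.
2. For any statement about subgroup efficacy, add an arm x time x characteristic term to the mixed model already planned for the primary anxiety outcome. Limit it to a short set of baseline characteristics named in advance, for example child age and sex. The set must be written down, because Efficacy evaluation refers to demographics without listing them. Report each interaction estimate with its 95% CI as exploratory.
3. Reconcile Efficacy evaluation with Covariates, so that age and sex are not assumed non-differential in one place and examined as efficacy predictors in the other.

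No new data are needed, but the interaction terms have a price. Power is low: the detectable interaction of about d = 0.95 is 1.9 times the 0.50 margin (0.95/0.50). Each added characteristic or outcome also adds a test. The set should therefore stay small, and no confirmatory subgroup claim should be made.

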#### Sample size

A minimum sample size of 138 children (69 per group) is needed to test the equivalence between two interventions that do not differ by more than the minimum expected effect size of *d* = 0.50, which is slightly larger than the recommended minimum practical effect size indicated by Ferguson [47]. This calculation is based on the two one-sided tests (TOST) procedure for determining equivalence as outlined by Lakens [48] and using the authors´ TOSTER package for R, assuming equal group allocation, alpha = 0.05, 80% power, and four measurements. This sample size is also sufficient to detect within-subject changes in anxiety scores of the same magnitude (*d* = 0.50) over four measurements (WebPower; [49]). With this sample and allowing for a substantial violation of sphericity, the achieved power is 97%. Finally, an *N* = 138 with four measurements is sufficient for growth mixture modeling [50]. With an attrition rate of 15% [19, 51], we will have to recruit approximately 165 parents at T0 to achieve the final intended sample size.

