Following Kennedy, Bilek [19], the attainment of diagnostic remission for both the principal diagnosis and all emotional disorder diagnoses at posttreatment and follow-up will be defined as the absence of the principal diagnosis and the absence of all emotional disorder diagnoses, respectively (i.e., ADIS-IV CSR < 4). A CGI-I score of 1 (*very much improved*) or 2 (*much improved*) at posttreatment or follow-up will be considered an indication of a meaningful reduction in the severity of emotional disorders and will be deemed indicative of a positive treatment response, consistent with the findings from other studies [19, 86].

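### An RCI of ±1.96 marks reliable change, not clinically significant change as the plan labels it

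*Protocol article*

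**What the plan says.** All of this is in the protocol article, Statistical methods, Efficacy evaluation.

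- **Purpose of the RCI:** "To examine for heterogeneous intervention response, we will calculate Reliable Change Indices (RCI) for all participants", at postintervention and at the 3-month follow-up.
- **Use of the RCI:** "The RCI will be calculated for all outcomes and correlated with demographics to examine for subgroup efficacy predictors".
- **Threshold:** "The cutoff for clinically significant change is generally accepted as" ±1.96, with a literature citation. The passage adds no normative range, end state or minimal important change.
- **Primary test:** "The primary equivalence testing will be the between-group difference TOST at postintervention and at 3 months". It does not involve the RCI.
- **Remission:** defined separately for the principal diagnosis and for all emotional disorder diagnoses. It "will be defined as the absence of the principal diagnosis and the absence of all emotional disorder diagnoses, respectively", with an ADIS-IV clinician severity rating (CSR) below 4.
- **Response:** a CGI-I score of 1 or 2, which "will be considered an indication of a meaningful reduction in the severity of emotional disorders".

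**The concern.** The RCI divides a person's change by the standard error of the difference between two imperfectly measured scores. A value beyond ±1.96 says that the change is unlikely to be measurement noise. It does not say that the child has reached a healthier range, lost a diagnosis or improved to a degree that a clinician would call meaningful. The plan nevertheless gives the threshold a clinical label.

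At stake is what can be said about a child who passes it. The same section already holds two clinical criteria, remission and CGI-I response. A child can pass ±1.96 on a questionnaire and meet neither. That child would be clinically significantly changed under one label and a non-remitter and non-responder under the others, and the plan has no rule relating the three.

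**Working it through.** **Inputs.** The cutoff ±1.96 and its label come from Efficacy evaluation. The article gives neither an RCI formula nor score reliabilities. I therefore use the standard form of the index and assume a reliability r between 0.70 and 0.90.

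**Step 1: what the plan's figure is.** RCI = (post − pre) / (SD × √(2(1 − r))). With no true change this is approximately standard normal, and P(|Z| > 1.96) = 0.0500. The plan's figure is thus reproduced as the two-sided 5% critical value for measurement error. No clinical quantity enters the formula.

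**Step 2: how much change it requires.** In SD units the threshold is 1.96 × √(2(1 − r)):

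| Assumed r | Change needed |
|---|---|
| 0.90 | 1.96 × √0.20 = 0.88 SD |
| 0.85 | 1.96 × √0.30 = 1.07 SD |
| 0.80 | 1.96 × √0.40 = 1.24 SD |
| 0.70 | 1.96 × √0.60 = 1.52 SD |

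The ratio of the extremes is 1.52 / 0.88 = 1.73. This spread is no defect of the RCI, since scaling by reliability is its purpose, and it remains after relabelling. It does show that the bar is set by the precision of the instrument and not by a clinical standard.

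**Step 3: reliable improvement without a clinical end state.** Suppose a child starts 2.0 SD above the normative mean and the functional cutoff lies midway, at 1.0 SD. With r = 0.90, a fall of 0.88 SD just reaches the RCI threshold and leaves the child at 2.0 − 0.88 = 1.12 SD, still above the cutoff.

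A simulation gives a sense of scale. It assumed a clinical mean 1.5 or 2.0 SD above the norm, a midway cutoff, a mean improvement of 0.5 or 1.0 SD, an SD of individual true change of 0.6, and r of 0.70, 0.80 or 0.90. Among children with reliable improvement, 28% to 55% did not also move from above the cutoff to below it. Every input is assumed, so this is an illustration and not a forecast for this trial.

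**Step 4: what is not touched.** The sample size rests on the equivalence margin, for "equivalence between two interventions that do not differ by more than the minimum expected effect size of" d = 0.50. With a true difference of zero, n per group = 2 × ((1.645 + 1.282) / 0.5)² = 68.5, rounded up to 69, or 138 in total as the plan states. The RCI does not enter it. It enters neither the primary two one-sided tests (TOST) nor the definitions of remission and response.

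**Step 5: whether remission can serve as the end state for everyone.** Participants and Participant selection admit children with subclinical anxiety, and a diagnosis requires a CSR of 4 or more. A child without a diagnosis has none to lose and would meet the remission rule at baseline. The RCI also covers parent measures, such as depressive symptoms, criticism and inconsistency, for which a child's diagnosis is not an end state. Remission alone therefore cannot be the added criterion.

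**The case against.** The strongest reply is that this is only a loose label on an exploratory analysis. The RCI is there to look at heterogeneity, and correlating it with demographics needs no cutoff. The sentence describes a convention. It does not say that children will be classified, that a rate will be reported or that arms will be compared on it. Clinical benefit is defined elsewhere in the section. How RCI classes are formed and tabulated may be set out in a fuller document.

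Most of this stands, and it limits the point. Two stronger readings are tempting and should not be drawn.

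- A reader might infer that the trial will misreport clinical benefit. The article does not support that. The primary conclusion comes from the TOST, remission and response have their own definitions, and no RCI-based rate is promised.
- A reader might infer that ±1.96 merges improvement with deterioration. It does not. The index is signed, and the two limits already separate the directions. What the passage leaves unstated is which sign means improvement on which scale. Higher is worse on the RCADS and CALIS, but better on positive affect, the CAMM and KIDSCREEN-10.

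What the reply does not remove is the statement itself. It is wrong as written, so this is not a detail left to another document. A cutoff also has little purpose except to classify people. The source cited for the convention is not at hand, but the point rests on how the index is built.

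**Conclusion.** The point holds as a correction of a mislabelled threshold, and it is minor. ±1.96 on the RCI identifies reliable change; the plan calls it clinically significant change and adds no clinical criterion. The change it demands is 0.88 to 1.52 SD for reliabilities of 0.90 to 0.70, which are assumed, as is the standard form of the index. The consequence is confined to children described by the RCI alone: such a child could be called clinically significantly changed while meeting neither of the plan's own clinical criteria. How many would be affected cannot be computed from the article.

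**What to change.** 1. Call ±1.96 the threshold for reliable change.
2. State for each scale which direction is improvement, and report three classes: reliably improved, no reliable change, reliably deteriorated.
3. On the child anxiety outcomes, reserve clinically significant change for reliable improvement together with a criterion already in the plan: diagnostic remission (CSR < 4) for children with a diagnosis at baseline, and CGI-I of 1 or 2 for children with subclinical anxiety. Say which of the two remission definitions is meant. Show the rate by baseline diagnostic status, because the criterion differs between the two groups.
4. For the parent and process measures, report reliable change only.

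The cost is a change of wording and one extra cross-tabulation. The ADIS-IV-C is already planned at posttreatment and follow-up, and CGI-I response is defined at the same two points. Design, sample size and data collection stay as they are. The downside is that the clinically significant rate may be lower than one based on the RCI alone.

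### The growth mixture analysis starts at two classes, so BIC/SABIC cannot favour a single trajectory, although the predictor analysis depends on heterogeneity being observed

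*Protocol article*

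**What the plan says.** All of the relevant text is in the protocol article, under Statistical methods, Efficacy evaluation, except for one sentence under Sample size.

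- Candidate models: the investigators will "evaluate various model specifications of" k "classes two through six, and using both fixed and random effects".
- Selection criteria: "parsimony, entropy approaching 1, lowest BIC/SABIC, and minimum class size > 10% of the sample". No numeric entropy threshold is given, and nothing says which index prevails if BIC and SABIC disagree.
- Follow-on analysis: "assuming that heterogeneous trajectories of anxious symptoms are observed, we aim to test the suitability of the collected demographic variables" as predictors of group membership.
- Sample size: N = 138 "with four measurements is sufficient for growth mixture modeling".

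No one-class growth model is named as a candidate or comparator. No conclusion is stated for the case in which no solution meets the criteria.

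**The concern.** The predictor analysis is conditional, so the authors accept that all children might follow one common course with ordinary variation around it. The way to check this in a mixture analysis is to compare the one-class model with the larger ones. Here the smallest model fitted already has two classes. Parsimony and BIC/SABIC can push the choice down to two and no further. The condition in front of the predictor analysis therefore has no fitted model behind it.

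If there is in truth one trajectory, the analysis can cut a continuous distribution into groups. It would then test age, sex and other demographic variables as predictors of those groups, and the result could be published as types of treatment course in children.

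**Working it through.** **Inputs from the protocol article.** N = 138 (69 per arm), four measurements, k = 2 to 6, smallest class above 10% (0.10 × 138 = 13.8, so at least 14 children).

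**The plan's own figure.** For two one-sided tests with a true difference of zero, margin d = 0.50, alpha 0.05 and 80% power, n per arm = 2 × ((z0.95 + z0.90)/0.50)² = 2 × ((1.645 + 1.282)/0.50)² = 68.5, rounded up to 69. The total is 138, with normal-approximation power 80.4%. The stated N reproduces. The article gives no figure for the class-selection step.

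**Inputs assumed, because the documents give no variances.** One mean trajectory with quadratic coefficients 0, −1.2 and 0.5; normal random intercept (variance 0.5) and slope (variance 0.3) with covariance −0.1; residual SD 0.6.

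**Criteria.** BIC = −2 lnL + q ln N, and SABIC = −2 lnL + q ln((N + 2)/24). In the random-effects model with shared covariance, q = 3k + (k − 1) + 4, so q = 7 for one class and 11 for two.

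**Random-effects models, 200 one-trajectory samples**

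| Rule | Result |
|---|---|
| Lowest BIC, k = 2 to 6 (as written) | two classes in 200 |
| Lowest BIC, k = 1 to 6 | one class in 200 |
| Lowest SABIC, k = 1 to 6 | one class in 110, more than one in 90 |
| Lowest BIC, k = 2 to 6, smallest class > 10% | two or more classes in 143 (71.5%); none admissible in 57 (28.5%) |

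The two-class BIC was on average about 13.4 points worse than the one-class BIC. That evidence against a second class is never seen if k = 1 is not fitted.

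**Why SABIC does not protect.** Going from one class to two adds 11 − 7 = 4 parameters. The BIC penalty is 4 × ln 138 = 19.7, so the average gain in 2 lnL was 19.7 − 13.4 = 6.3. The SABIC penalty is 4 × ln(140/24) = 7.1, leaving the two-class model only about 7.1 − 6.3 = 0.7 worse (from unrounded values) on average.

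**Entropy.** The share of samples with at least one solution of two or more classes that passed the size rule and also reached an assumed entropy cut-off was 70/200 (35%) at 0.6, 23/200 (11.5%) at 0.7 and 5/200 (2.5%) at 0.8.

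**Fixed effects only, 20 samples.** With k = 1 available, BIC still chose three classes in 17 and four in 3. The two-class BIC was on average about 109 points better than the one-class BIC. Without random effects, ordinary differences between children can only be absorbed by adding classes.

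**Sensitivity to the assumptions.** A second set of 200 one-trajectory samples used a shared unstructured covariance and k up to 4. BIC chose one class in 200 with k = 1 included; without it, two classes in 199 and three in 1. At least one solution with two or more classes passed the size rule in 98%, against 71.5% above. The BIC result is stable across the two set-ups. The share passing the size rule is not.

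**The case against.** A reader might infer that the written rule must report heterogeneous trajectories whenever all children share one. The documents do not support that. The rule has four criteria, and two of them, class size and entropy, can reject every solution. On class size alone this happened in 57 of 200 samples, and a strict entropy cut-off of 0.8 would reject nearly all random-effects solutions. The conditional wording ("assuming that heterogeneous trajectories of anxious symptoms are observed") also shows that homogeneity was foreseen. This part of the objection stands and limits the claim. It does not remove it, because the article sets no entropy threshold and does not say that failure of every solution means one trajectory.

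Three further arguments deserve an answer.

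- The article condenses a fuller plan that might hold a one-class baseline. But the range of k is not left open: the article states it, and its lower bound does not fit the stated condition.
- A repeated-measures linear mixed model with linear and quadratic time effects is planned for each outcome, so readers will see an average course in any case. That limits the harm, but the article plans no comparison of that model with the mixture models.
- Trajectory classes are not among the aims listed under Objectives, and demographic predictors are also examined through reliable change indices. This is right, and it is why the point is one of moderate weight.

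It would also go too far to say that adding k = 1 cures the problem by itself. With k = 1 present, SABIC still chose more than one class in 90 of 200 samples, and the fixed-effects-only models always did.

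**Conclusion.** The point holds in limited form. As written, the BIC/SABIC comparison cannot favour a single trajectory, while the predictor analysis depends on heterogeneity being observed. That follows from the text and needs no assumption.

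Its size depends on assumed variances. In one-trajectory data at N = 138 with random effects, BIC over the stated range chose two classes in 200 of 200 samples, and one class in 200 of 200 once k = 1 was allowed. After the class-size rule, a false split remained available in 71.5% to 98% of samples across the two set-ups. Any entropy threshold applied in practice would lower these shares by an amount the article does not fix. All simulations used one-trajectory data, so they say nothing about how often BIC would miss a real second class.

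The analysis affected is a supplementary look at heterogeneity. The primary equivalence test and the sample size of 138 do not depend on k. The change should be made before the data are analysed.

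**What to change.** 1. Change the candidate set to k = 1 to 6 in each specification.
2. Let BIC in the random-effects specification decide one class versus more. Do not base this decision on SABIC alone or on the fixed-effects-only model.
3. Use entropy and the 10% class-size rule only to choose among solutions with two or more classes.
4. If k = 1 has the lowest BIC, or no solution with two or more classes meets the criteria, report a single trajectory and do not run the class-membership predictor analysis.

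The cost is one extra model fit per specification and one sentence in the plan. No further data or children are needed.
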